#### Solicited AEs:

All solicited AEs observed within 7 d of immunization are assumed by default to be related to the vaccine. The relationship between all unsolicited AEs/SAEs and the vaccines will be determined by the investigator.

✓ Local reactions

Pain, induration, swelling, rash, redness, and pruritus.

Systemic reactions

Fever, fatigue/weakness, decreased appetite, nausea, vomiting, diarrhea, allergy, myalgia, and arthralgia.

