### 3.5 Adverse Event Grading Criteria

Post-immunization systemic and local reactions are assessed in accordance with the Guidelines for Classification of Adverse Events in Clinical Trials of Preventive Vaccines (2019 edition) by National Medical Products Administration.

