**Table 1. Local reaction grading scale**

| Symptom/Sign                   | Grade 1                                                            | Grade 2                                                  | Grade 3                                                                                                                                     | Grade 4                                                         |
|--------------------------------|--------------------------------------------------------------------|----------------------------------------------------------|---------------------------------------------------------------------------------------------------------------------------------------------|-----------------------------------------------------------------|
| Pain                    | Does not affect or slightly affects activities of the limbs | Affects activities of the limbs                          | Affects activities of daily life                                                                                                            | Loss of self-care abilities or hospitalization           |
| Induration and swelling | Diameter of <2.5 cm                                                | Diameter of ≥2.5cm or area of <50 cm  | area of ≥50 cm  or ulcers or secondary infections or phlebitis or aseptic abscess or wound drainage | Abscess, exfoliative dermatitis, dermal or deep tissue necrosis |

|                         |                                                                                      |                                                                                  |                                                                                                                                                   |                                                                 |
|-------------------------|--------------------------------------------------------------------------------------|----------------------------------------------------------------------------------|---------------------------------------------------------------------------------------------------------------------------------------------------|-----------------------------------------------------------------|

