| Rash and redness | Diameter of <2.5 cm                                                                  | Diameter of $\geq 2.5$ cm or area of <50 cm                   | area of $\geq 50$ cm  or ulcers or secondary infections or phlebitis or aseptic abscess or wound drainage | Abscess, exfoliative dermatitis, dermal or deep tissue necrosis |
| Pruritus         | Pruritus at the injection site that resolves within 48 on its own or after treatment | Pruritus at the injection site that does not resolve within 48 h after treatment | Affects activities of daily life                                                                                                                  | NA                                                              |

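### The Grade 2 size rule for four local reactions in Table 1 is true for every size, so it overlaps Grades 1 and 3 and leaves their descriptive severity split open

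*Combined protocol and SAP*

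**What the plan says.** Section 3.4 (Solicited AEs) lists six solicited local reactions: "Pain, induration, swelling, rash, redness, and pruritus". Section 3.5 grades them in Table 1. Pain and pruritus are graded without any size limit. The other four share two rows, induration with swelling and rash with redness, and both rows print the same size limits:

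- Grade 1: "Diameter of <2.5 cm".
- Grade 2: "Diameter of ≥2.5cm or area of <50 cm" in the induration and swelling row, and "Diameter of $\geq 2.5$ cm or area of <50 cm" in the rash and redness row. In both, the unit of area is square centimetres.
- Grade 3: "area of ≥50 cm 2 or ulcers" and "area of $\geq 50$ cm 2 or ulcers" respectively, followed in each row by further complications that do not depend on size.
- Grade 4: no size limit.

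Section 3.5 opens by naming an external source: "Post-immunization systemic and local reactions are assessed in accordance with the Guidelines for Classification of Adverse Events in Clinical Trials of Preventive Vaccines" (2019 edition). The text of that guideline is not among the documents. Nothing supplied says which grade applies when a reaction meets two.

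**The concern.** Grade 2 should be the band between Grades 1 and 3, with a lower limit on diameter and an upper limit on area. Joined by *or*, either limit is enough, so small reactions qualify through the area limit and large ones through the diameter limit. The cell then bounds nothing, and its neighbours on both sides fall inside it.

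The synopsis names safety in the study objective, section 3.1 says the design evaluates safety, and section 6 defines a safety set. Table 1 is the only severity scale for local reactions that the protocol prints. If its wording is followed as it stands, the division of induration, swelling, rash and redness into Grades 1, 2 and 3 depends on a choice that the plan does not record.

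**Working it through.** The plan states no figure here that could be reproduced. The check is whether the printed limits give each size exactly one grade.

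**Inputs** (Table 1, both rows): Grade 1 if d < 2.5 cm; Grade 2 if d ≥ 2.5 cm *or* A < 50 cm²; Grade 3 on size if A ≥ 50 cm². Here d is the diameter, taken as the longest extent, and A is the area.

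**Step 1: put the limits on one scale.** For a circle, A = πd²/4.
- d = 2.5 cm gives A = π × 6.25 / 4 = 4.91 cm².
- A = 50 cm² gives d = √(200/π) = 7.98 cm.

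**Step 2: when does the Grade 2 rule fail?** Only when both parts are false, that is d < 2.5 cm and A ≥ 50 cm². A circle under 2.5 cm has an area below 4.91 cm², about a tenth of 50 cm², and no other flat shape with the same longest extent has a larger area. The rule therefore never fails. Circles from 0.001 to 20 cm in steps of 0.001 cm (20,000 sizes), and ellipses with a long axis up to 29.9 cm, all met Grade 2. Measuring across the short axis instead changes little: an ellipse 2.5 cm wide reaches 50 cm² only at a length of 4 × 50 / (π × 2.5) = 25.5 cm.

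**Step 3: grades met by circular reactions.**

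| Diameter | Area | Grades met, *or* as printed | Grades met, *and* |
|---|---|---|---|
| 0.5 cm | 0.20 cm² | 1 and 2 | 1 |
| 2.49 cm | 4.87 cm² | 1 and 2 | 1 |
| 2.5 cm | 4.91 cm² | 2 | 2 |
| 6 cm | 28.27 cm² | 2 | 2 |
| 7.97 cm | 49.89 cm² | 2 | 2 |
| 7.98 cm | 50.01 cm² | 2 and 3 | 3 |
| 10 cm | 78.54 cm² | 2 and 3 | 3 |

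As printed, only diameters from 2.5 cm to just under 7.98 cm receive a single grade. With *and*, every circle and ellipse tested fell in exactly one grade.

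**Step 4: would a precedence rule rescue the printed text?** Both rules below are assumptions, since the documents state none.
- Highest grade met: Grade 3 on size holds exactly the reactions of 50 cm² or more, as its own cell intends. All reactions under 2.5 cm become Grade 2, and Grade 1 on size is empty.
- Lowest grade met: the boundary between Grades 1 and 2 is as printed, but a reaction of 50 cm² or more is Grade 2, and none is Grade 3 on size alone.

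Each rule keeps one boundary and loses the other. Only letting Grades 1 and 3 override Grade 2 keeps both, and that is the *and* reading under another name.

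**The case against.** The strongest reply is that the meaning can be recovered from the row. Grades 1 and 3 print their own limits, 2.5 cm and 50 cm², which are the two numbers in the Grade 2 cell. A sensible grader would see three adjoining bands and would have to ignore the Grade 1 cell to leave it empty. That stands as an account of the likely intent, and it makes the correction easy to identify. It does not make the printed rule correct, because the grader must override a connector that appears in both rows.

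A second reply is that section 3.5 defers to a national guideline, which may settle the matter. That cannot be checked here. If the guideline prints the same connector, the overlap remains; if it differs, Table 1 departs from the source it claims to follow. Both cases call for reconciliation.

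A third reply concerns weight. The hypotheses and the outcomes in sections 1.1 and 1.2 are immunogenicity measures, the termination criteria in section 4.3 use no grade, and the supplied text has no endpoint or test based on grade. All of this stands, and it limits the point to descriptive safety reporting.

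A reader might also infer three stronger things that the documents do not support:
- That mild, moderate and severe local-reaction counts as a whole are undetermined. Pain and pruritus use no size rule, the connector does not bear on the complications listed under Grade 3 or on Grade 4, and Grade 3 on size is intact if the highest grade is taken.
- That grading would differ between arms because the trial is open-label. Both arms use one table, and nothing indicates that the connector would be read differently by arm.
- That reactions have in fact been misgraded. The documents contain no local-reaction results and do not say how staff read the cell.

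**Conclusion.** The Grade 2 size rule is wrong as written in both rows: it is true for every size and overlaps Grade 1 below 2.5 cm and Grade 3 from 50 cm² upward. Followed literally, it either empties Grade 1 on size or removes Grade 3 on size alone, depending on a precedence rule that the supplied text does not state.

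The consequence is narrow. It touches the descriptive split by grade of four of the six solicited local reactions. Whether a reaction occurred is unaffected, as are pain, pruritus, the Grade 3 criteria that do not depend on size, Grade 4 and all immunogenicity outcomes. The empty grades are the logical ends of two literal readings, not an estimate of how many children were misclassified; no such number can be drawn from these documents.

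The conclusion assumes that diameter means the longest extent and that no precedence rule exists outside the supplied text. The unseen guideline could supply one, but neither taking the highest nor taking the lowest grade would repair both boundaries.

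**What to change.** Reconcile the Grade 2 cell in both rows of Table 1 with the Grade 1 and Grade 3 cells beside it and with the 2019 national guideline named in section 3.5. Joining the two limits with *and* makes the printed limits mutually exclusive; the sponsor should confirm that wording against the guideline. Apply the same size bands in both arms, and state which grade is assigned if a reaction still meets more than one, for example a small reaction with a listed complication.

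Where diameter or area was recorded, check the assigned grades against the corrected bands and amend any that differ.

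The text change is one word in two cells. The check needs no new data if sizes were captured, but the documents do not confirm this: section 3.4 says only that solicited events are entered on diary cards. Where only a grade was recorded, the check cannot be made, and the safety report should say how the Grade 2 cell was applied.

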**Table 4. Systemic reaction grading scale**

| Symptom/Sign                               | Grade 1                                                                                                      | Grade 2                                                                                      | Grade 3                                                                                                   | Grade 4                                                                                       |
|--------------------------------------------|--------------------------------------------------------------------------------------------------------------|----------------------------------------------------------------------------------------------|-----------------------------------------------------------------------------------------------------------|-----------------------------------------------------------------------------------------------|
| Fever * [axillary temperature (°C)] | 37.3 to <38.0                                                                                                | 38.0 to <38.5                                                                                | 38.5 to <39.5                                                                                             | $\geq 39.5$ for 3 d                                                                           |
| fatigue/weakness                    | Does not affect activities of daily life                                                                     | Slightly affects activities of daily life                                                    | Severe myalgia, severely affects activities of daily life                                                 | Emergency care or hospitalization                                                             |
| decreased appetite                  | Decreased appetite, but not reduced food intake                                                              | Appetite decreased and food intake decreased, but body weight did not decrease significantly | Decreased appetite and weight                                                                             | Interventions are needed (such as gastric tube feeding, parenteral nutrition)                 |
| Nausea                              | Transient (<24 h) or intermittent and normal food intake                                              | Persistent nausea leading to decreased food intake (24–48 h)                                 | Persistent nausea leading to nearly no food intake (>48 h) or requires intravenous rehydration     | Life-threatening (such as hypotension shock)                                                  |
| Vomiting                            | 1–2 times/24 h and does not affect activity                                                           | 3–5 times/24 h or limited activities                                                  | >6 times/24 h or requires intravenous rehydration                                                  | Requires hospitalization or other routes of nutrient delivery due to hypotension shock |
| Diarrhea                            | Mild or transient, 3–4 times/d, abnormal stool property, or mild diarrhea that persists for less than 1 week | Moderate or persistent, 5–7 times/d, abnormal stool property, or diarrhea that lasts >1 week | >7 times/d, abnormal stool property, or hemorrhagic diarrhea, orthostatic hypotension, electrolyte | Hypotension shock, requires hospitalized treatment                                            |

|                                     |                                                       |                                                                                                          |                                                                                          |                                                                                      |
|-------------------------------------|-------------------------------------------------------|----------------------------------------------------------------------------------------------------------|------------------------------------------------------------------------------------------|--------------------------------------------------------------------------------------|
|                                     |                                                       |                                                                                                          | imbalance,
requires >2 L
intravenous infusion                                      |                                                                                      |
| Acute allergic reactions     | Local urticaria (blister), does not require treatment | Local urticaria, requires treatment or mild angioedema, does not require treatment                | Extensive urticaria or angioedema requiring treatment or mild bronchospasm | Anaphylactic shock or life-threatening bronchospasm or laryngeal edema |
| Myalgia (non-injection site) | Does not affect activities of daily life              | Slightly affects activities of daily life                                                                | Severe myalgia, severely affects activities of daily life                                | Emergency care or hospitalization                                                    |
| Arthralgia                   | Mild pain, does not affect function                   | Moderate pain; requires analgesics and/ or pain affects function but not activities of daily life | Severe pain; requires analgesics and/ or pain affects activities of daily life    | Disabling pain                                                                       |

Clinical abnormalities not mentioned in the above table can be graded according to the following adverse reaction criteria:

| Grade 1                                                           | Grade 2                                                                                                              | Grade 3                                                                                                            | Grade 4                                                                                                                               | Grade 5 |
|--------------------------------------------------------------------------|-----------------------------------------------------------------------------------------------------------------------------|---------------------------------------------------------------------------------------------------------------------------|----------------------------------------------------------------------------------------------------------------------------------------------|----------------|
| Mild, short-term discomfort (<48 h), does not require medical treatment; | Mild-moderate to moderate, limits activities of daily life, does not require or only requires minimal medical intervention; | highly limits activities of daily life, requires daily care, requires medical treatment, and may require hospitalization; | Life-threatening, extremely limits activities of daily life, highly requires daily care, and requires medical treatment and hospitalization. | Death          |

### 3.6 Causality Assessment of Adverse Event

The investigator should have measures in place to judge the causal relationship between solicited/unsolicited AEs and immunization, to identify immunization-related SAEs, and to suspend or terminate the clinical trial in a timely manner in order to minimize damages to the subjects.

General rules for causality assessment:

- ✓ **Definitely related:** Evidence of investigational vaccine immunization; AE follows a reasonable temporal sequence from immunization with the investigational vaccine; occurrence of AE is more reasonably explained by the investigational vaccine than other reasons; AE is observed after repeated immunization with the investigational vaccine; AE is consistent with what is known about this type of vaccine.
- ✓ **Probably related:** Evidence of investigational vaccine immunization; AE follows a reasonable temporal sequence from immunization with the investigational vaccine; occurrence of AE is more reasonably explained by the investigational vaccine than other reasons.
- ✓ **Possibly related:** Evidence of investigational vaccine immunization; AE follows a reasonable temporal sequence from immunization with the investigational vaccine; occurrence of AE may be explained by the investigational vaccine or other reasons.
- ✓ **Possibly unrelated:** Evidence of investigational vaccine immunization; AE is more likely caused by other reasons; AE is absent or undetermined after repeated immunization.
- ✓ **Definitely unrelated:** Absence of investigational vaccine immunization; or AE does not follow a reasonable sequence from immunization with the investigational vaccine; or AE is caused by other obvious reasons.

### 3.7 Sample Size Estimation

The sample size was estimated using an objective performance criteria method. Assuming the target value was 70% of the seroconversion rate of anti-pertussis in the co-purified DTaP group after vaccination, with a two-sided  $\alpha$  of 0.05, a power of 90%, and a potential loss to follow-up of 15%, we estimated at least a sample size of 240 participants per group.

## 4. INCLUSION, EXCLUSION, TERMINATION, AND WITHDRAWAL CRITERIA

### 4.1 Inclusion Criteria

Subjects must meet the following criteria to be included in this study:

- 1) Age 6 years on the day of enrollment;
- 2) has signed and dated the informed consent form;

- 3) able to participate in all scheduled visits and comply with all study procedures (E.g. Completion of diary card and participation in visits);
- 4) received 4 doses of diphtheria, tetanus, and pertussis vaccine; not vaccinated with diphtheria, tetanus, and pertussis immunization products in the past 3 years;
- 5) had no history of pertussis, diphtheria, or tetanus;
- 6)  $\geq 14$  d since the last vaccine immunization;
- 7) body temperature  $\leq 37.3^{\circ}\text{C}$  confirmed by medical history and clinical examination before entering into this study.

## 4.2 Exclusion Criteria

### Exclusion criteria for first dose

- ✕ allergy to any ingredient of the vaccine;
- ✕ past history of serious allergies to any immunization;
- ✕ medical or family history of convulsion, epilepsy, cerebral diseases and mental diseases;
- ✕ patient with immunodeficiency, has received immunosuppressants (oral steroids) during the treatment of malignant tumors or has HIV-induced immune impairment, or presence of congenital immune disease in close family member;
- ✕ injection of non-specific immunoglobulin within 1 month before enrollment;
- ✕ has acute febrile and infectious diseases;
- ✕ definite diagnosis of thrombocytopenia or history of other coagulopathy that may cause subcutaneous injection to be contraindicated;
- ✕ patient with serious chronic disease or in the acute phase of a chronic disease, or with uncontrolled hypertension or diabetes;
- ✕ various infectious, purulent, and allergic skin diseases;
- ✕ any other conditions that the investigator determines may impact the trial assessments.

## 4.3 Termination and Removal Criteria

Subject participation will be terminated early if any of the following is observed:

- protocol violations that render the investigator to believe that participation should be terminated;
- subject requests for trial withdrawal;
- intolerable AE, regardless of its relationship with the investigational vaccine;

- subject's health conditions do not allow him/her to continue participating in the trial;
- any other reasons determined by the investigator.

